### Health economic evaluation

Healthcare resource use (contacts with primary, community and secondary care, hospitalisations, procedures and medications) will be extracted from patient medical records. Service resource use not available from files and wider services (e.g. of voluntary sector and social care) will be collected using a modified Client Services Receipt Inventory (CSRI) [63] at 0, 6 and 12 months, asking about the previous 6-months. The CSRI has been modified based on the population in our feasibility study to include the range of services they may use (e.g. podiatry, opticians, hearing aids, dental care, physiotherapy, exercise classes, day care, etc.). Health and social care resource use will be costed using nationally published sources (PSSRU [68], NHS Reference Costs [69] and the British National Formulary [70]). We will additionally ask about unpaid and paid (state and out-of-pocket) carer time for specific activities of daily living, using an adapted iMTA Valuation of Informal Care Questionnaire (iVICQ) [60]. This will be costed as the cost of face-to-face local authority-funded homecare worker time to reflect the fact that if this care were to be reduced homecare workers would be the alternative to unpaid carers providing this assistance.

Intervention costs (including staff training, administration, supervision and delivery) will be included in the costs of the intervention group.

### Process evaluation

The process evaluation will collect quantitative and qualitative data alongside the main trial. Feedback on service delivery (e.g. fidelity) will not be given to service providers or other team members until after trial completion. An independent researcher will carry out up to 40 semi-structured audio-recorded interviews with participants receiving the service, service providers and other stakeholders, using topic guides developed with our public and patient involvement and engagement (PPIE) representatives and stakeholders from our implementation group. We will additionally explore the impact of remotely delivering the service in the time of Covid-19 and its influence upon participant and provider experiences.

HomeHealth workers will keep an ongoing record of service delivery process data, including number of appointments attended, modality, technical issues experienced if delivering remotely, duration and reasons for non-attendance. Goals will also be recorded, and will be coded into mobility, psychological, social, memory, nutrition or other. We will ask providers to rate progress towards achieving goals, including 0–2 ratings for each SMART goal (0 = no progress, 1 partially met/some progress, 2 = met/exceeded goal) and goal attainment scaling for outcome goals (from -2 (much less than expected progress) to + 2 (much more than expected progress) [71]). Fidelity will be assessed through fidelity checklists, developed for this intervention and based on what should be included at each appointment. These will be completed after each appointment by HomeHealth workers. We will record all audio appointments, and independently verify fidelity using the same checklist by a trained rater, who will check recordings for all appointments from 10% individuals receiving the intervention.

We will also utilise trial data to explore mechanisms of impact, including demographic data to assess reach and outcome data to assess whether setting goals on one topic will affect the hypothesised linked outcome (e.g. psychological goal and psychological distress scores).

### Sample size

We are aiming to recruit a sample size of 386 people (193 per arm). This will provide 90% power at the 5% significance level to detect a minimum clinically important difference of 1.85-points [72] in the BI, with a standard deviation (SD) of 5. We found a SD of 3 in the feasibility RCT, however in frail populations larger SDs have been reported [20, 22] so we have conservatively assumed a larger SD. Using 90% power and 5% significance level, this would require 308 people (154 per group). Attrition was minimal (6%) over 6 months in our feasibility study, however other studies have reported higher attrition rates with longer follow-up [8] so we have conservatively assumed 20% attrition over 12 months. The first six months will form a pilot phase based on site-specific and overall recruitment rates (target red < 80, amber 80–159, green 160 +), with measures put in place if we are not recruiting at ‘green’.

We have not adjusted for clustering by therapist (HomeHealth worker) as we anticipated that this will be minimal and non-significant. No trials in those with mild frailty have reported intraclass correlation coefficients (ICCs) for therapist clustering, only clustering by GP practice in cluster RCTs in older community-based general populations [73]. Unpublished PhD thesis data examining therapist effects in a secondary analysis of a cluster exercise trial in older people [74] did not find significant clustering by therapist (ICC 0.01, *P* = 0.54).

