### Statistical methods

A detailed statistical analysis plan, including the health economic analysis, will be developed a priori and reviewed and approved by the Trial Steering Committee. All analyses will be by intention to treat. As missing data in the feasibility study were low and there are few gains to multiple imputation in RCTs [75, 76], imputation will not be used. We will descriptively summarise participants’ baseline characteristics using appropriate summary statistics (mean and SD, median and interquartile range or proportions) by randomised group.

The primary outcome (BI score at 12 months) will be analysed using linear mixed models, including 6 and 12-month data, controlling for baseline BI score and site (the stratification variable). Assumptions will be checked and appropriate transformations or analogous models will be used if the assumptions of linear models are violated. The ICC will be reported. Continuous secondary outcomes will be analysed using similar linear mixed models to the primary outcome, including 6 and 12-month data and controlling for outcome baseline score and site. Dichotomous outcomes (death and exhaustion) will be analysed using logistic regression. Falls will be analysed using Poisson regression or an analogous alternative if the assumptions for Poisson are not met. If it is not possible to use Poisson regression or an analogous alternative, then we will consider dichotomising falls and analysing in a similar way to other dichotomous outcomes. If there are too few events to perform statistical modelling for falls or the other dichotomous outcomes, they will be reported descriptively.

We will examine baseline predictors of missingness for the primary outcome and include any significant predictors of missingness in a supportive analysis to restore the missing at random assumption using a similar model to the primary analysis. All analyses will be complete case. We will also perform a complier average causal effects (CACE) analysis after unblinding using a threshold dosage of 3 + sessions for compliance to determine the average treatment effect of participants who would have adhered to the protocol regardless of how they were randomised.

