For the process evaluation, we will carry out a number of exploratory analyses, including whether those who get a therapeutic dose of HomeHealth (3 + sessions) have higher BI at 12 months; whether choice of goal impacts on related outcomes (e.g. social goal and UCLA-3 score) and whether progress towards goals is associated with higher BI scores. If sufficient data are available, we will explore the impact of remote delivery vs. face to face delivery on outcomes. We will descriptively summarise service delivery data (e.g. appointments attended) and compare the demographics of those recruited to the expected population to assess intervention reach. Qualitative data will be analysed using codebook thematic analysis [77], involving multiple multidisciplinary team members (including Patient and Public Involvement and Engagement (PPIE)), and barriers and facilitators to implementation will be explored using Normalisation Process Theory [78].

For the health economic analysis, we will calculate the mean incremental cost per quality adjusted life years gained (QALYs) using EQ-5D-5L and the relevant UK tariff. QALYs will be calculated from the EQ-5D-5L as the area under the curve adjusting for baseline [74] with site as a fixed effect in line with the analysis of the primary outcome. We will also report Years of Full Capability (YFC) using ICECAP-O and its respective tariff for the duration of the trial. YFC will be calculated according to the most current guidance [79]. The primary analysis will be the incremental cost per QALY gained from a health and personal social services cost perspective, with secondary analyses reporting the incremental cost per YFC gained, and calculating incremental costs from a wider cost perspective to capture the impact on carers and any patient/carer out of pocket costs for health and social care. Means and 95% confidence intervals will be based on bootstrapped results. We will adjust difference in total cost at 12 months by baseline values [80] with site as a fixed effect and a random effect for therapist clustering.

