### Limitations

As HomeHealth is a behaviour change intervention, participants cannot be blinded to arm allocation, which may bias participant reported outcomes. Researchers carrying out assessments and key trial management staff will be blinded to arm allocation to reduce the risk of bias. Systems and strategies to maintain blinding will be put in place (e.g. remote outcome assessments with an alternative blinded researcher from another site, where a researcher becomes accidentally unblinded during the course of the study).

HomeHealth showed promise of effectiveness in the initial feasibility study [33]. However, it should be noted that a number of adaptations were needed for trial processes and the intervention in light of the Covid-19 pandemic, including making provisions for remote intervention delivery and remote assessments. The context of the trial also changed due to the pandemic (e.g. TAU, including access to routine services, and levels of social isolation have changed). Our process evaluation will explore the impact of this, in order to inform future recommendations.

A larger number of intervention providers will be delivering the HomeHealth service than in the feasibility study, which may affect consistency across participants or sites. In order to reduce the risk of drift, HomeHealth workers will have regular case-based supervision from a centrally located Team Leader and we will calculate ICCs to explore therapist effects. Fidelity of delivery will also be explored in the process evaluation.

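### The primary Barthel and QALY models name no HomeHealth worker term although the cost model has one; if worker clustering exists and the term is left out, the primary confidence interval is somewhat too narrow

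*Protocol article*

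**What the plan says.** Four places in the protocol article bear on this.

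- **Sample size.** The calculation makes no allowance for workers: "We have not adjusted for clustering by therapist (HomeHealth worker) as we anticipated that this will be minimal and non-significant". The section reports that no trial in mild frailty has published a therapist ICC. It then relies on unpublished thesis data from a cluster exercise trial in older people, which "did not find significant clustering by therapist (ICC 0.01", P = 0.54).
- **Statistical methods, primary outcome.** BI at 12 months is analysed by a linear mixed model using the 6- and 12-month data, "controlling for baseline BI score and site (the stratification variable"). No worker term is named. The section also promises to report an ICC, without saying at which level.
- **Statistical methods, health economics.** QALYs are adjusted for baseline and site, expressly in line with the primary analysis. The 12-month cost difference is adjusted for baseline "with site as a fixed effect and a random effect for therapist clustering". Costs and QALYs are then linked by seemingly unrelated regression.
- **Limitations.** "A larger number of intervention providers will be delivering the HomeHealth service than in the feasibility study", and the authors say this may affect consistency. Their response is supervision, fidelity checks and exploratory ICCs for therapist effects.

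**The concern.** Participants in the HomeHealth arm share workers; participants in the control arm do not. If some workers achieve better outcomes than others, outcomes within a caseload are correlated. The intervention-arm mean is then less precise than a model with only baseline and site assumes. The primary confidence interval would be too narrow and the chance of a false positive above 5%.

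The plan treats this as worth modelling for costs but names nothing for BI or QALYs, and gives no reason for the difference. A non-significant P value for an ICC does not show that the ICC is zero. The effect on precision also depends on caseload, which the article does not give: a small ICC with a large caseload can matter.

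**Working it through.** **Inputs from the Sample size section:** difference 1.85, SD 5, 5% significance (taken as two-sided), 90% power, 20% attrition, therapist ICC 0.01. **Assumed:** k = 4 to 15 HomeHealth workers with equal caseloads, because the article gives neither number nor caseload.

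**1. Reproduce the plan's figure.** n per arm = 2 × (1.96 + 1.2816)² × 5² / 1.85² = 153.5, so 154 per arm and 308 in total, as the protocol states ("Using 90% power and 5% significance level, this would require 308 people (154 per group")). Allowing for attrition, 154 / 0.80 = 192.5, so 193 per arm and 386 in total. With 154 per arm the standard error is 5 × √(2/154) = 0.570, and power is Φ(1.85/0.570 − 1.96) = 90.1%. The formula leaves almost no slack.

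**2. Add clustering in the HomeHealth arm only.**

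- Caseload analysed: m = 154/k
- Design effect in that arm: DE = 1 + (m − 1) × ICC
- SE of the difference: 5 × √((DE + 1)/154)
- Power: Φ(1.85/SE − 1.96)
- Factor by which the true SE exceeds the SE ignoring workers: f = √((DE + 1)/2)
- True type I error of a nominal 5% test that ignores workers: 2 × [1 − Φ(1.96/f)]

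Example with k = 6: m = 25.7; DE = 1 + 24.7 × 0.01 = 1.25; SE = 0.604; power = Φ(3.063 − 1.96) = 86.5%; f = 1.06; type I error 6.4%.

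Results at ICC 0.01:

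| Workers | Caseload | DE | f | Power | Type I error if omitted |
|---|---|---|---|---|---|
| 4 | 38.5 | 1.38 | 1.09 | 84.6% | 7.2% |
| 6 | 25.7 | 1.25 | 1.06 | 86.5% | 6.4% |
| 8 | 19.2 | 1.18 | 1.045 | 87.5% | 6.1% |
| 10 | 15.4 | 1.14 | 1.035 | 88.0% | 5.8% |
| 15 | 10.3 | 1.09 | 1.02 | 88.8% | 5.5% |

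Applying the design effect to both arms would exaggerate the loss (79.1% instead of 84.6% power with 4 workers), because control participants have no worker.

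**3. Offsets to the power loss.** The formula takes no credit for the planned baseline adjustment. Multiplying the SE by √(1 − r²), with r an assumed correlation between baseline and 12-month BI and the ICC held at 0.01, gives for 4 to 15 workers:

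- r = 0.3: power 88% to 91%
- r = 0.5: power 93% to 96%

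With the feasibility SD of 3 in place of 5, and no baseline adjustment, power exceeds 99%.

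**4. The offsets do not repair the type I error.** At a given ICC, f contains neither the SD nor the difference, so a smaller SD leaves the inflation unchanged. If worker variance is unrelated to baseline BI, adjustment shrinks only the residual and makes the ICC slightly larger. Worker variance is 0.01 × 25 = 0.25; at r = 0.5 the adjusted total variance is 25 × 0.75 = 18.75, and 0.25/18.75 = 0.013.

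**The case against.** The strongest reply is that the article does not say the primary analysis ignores workers. The sentence declining to adjust stands under Sample size and governs only that calculation. The primary model is a mixed model, an ICC will be reported, therapist ICCs will be explored, and full model detail is deferred to an analysis plan that is not shown. This stands in part: a worker effect may yet be fitted. But the article lists its adjustments for BI, aligns QALYs with them, and names the therapist effect only for costs. The promised ICC has no stated level, and a model with two follow-up times yields a within-participant ICC anyway. Reporting or exploring an ICC does not widen the confidence interval.

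The second reply is that the sample-size decision was disclosed and reasoned, with cautious choices elsewhere: SD 5 against 3 observed, and 20% attrition against 6% seen over 6 months. That stands. A reader might infer that the trial will fail to reach 90% power. The documents do not support this: the shortfall appears only in an unadjusted two-means formula with an assumed number of workers, and a moderate baseline correlation or a smaller SD removes it.

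A reader might also bring in a larger ICC, such as 0.05, to show a severe effect. No such value appears in the article, so it carries no weight here.

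**Conclusion.** The point holds in a conditional form. As described, the primary BI and QALY models carry no HomeHealth worker term, the cost model does, and the evidence offered for treating clustering as negligible is thin. If the true ICC is above zero and the term is omitted, the standard error is understated: by a factor of 1.02 to 1.09 at ICC 0.01 with 15 to 4 workers, for a true type I error of about 5.5% to 7.2%. On the protocol's own formula power falls to between 89% and 85%, a loss of about 1 to 5 percentage points that baseline adjustment or an SD below 5 could offset.

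It would go too far to say that the standard errors are too small as a matter of fact. That needs both a non-zero ICC and a final model without the term, and the article settles neither. The figures rest on the assumed worker numbers, equal caseloads and a normal approximation; they are for BI, and the article gives no ICC for QALYs. The effect at the cited ICC is modest, so this should be fixed but is not critical.

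**What to change.** 1. In the primary BI model and the QALY model, include a random effect for HomeHealth worker in the intervention arm, consistent with the therapist effect already planned for costs. State at which level the promised ICC is reported.
2. In the sample-size text, either say that the 90% assumes a therapist ICC of zero and no baseline adjustment, or show power at ICC 0.01 over a range of worker numbers. Give the planned number of workers.
3. Do not recruit more participants on this account.

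The cost is one more variance term, a slightly wider confidence interval and a few sentences of text. Worker identity reveals allocation, so the model should be fixed in advance and fitted after database lock. The choice of degrees-of-freedom method, residual variance structure and bootstrap scheme can be left to the analysis plan.

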### Participant timelines

Participants will be involved in the RCT for 12 months. Participants will be randomised within four weeks of completing the baseline assessment to HomeHealth or TAU and 6 months (i.e. end of intervention) and 12 months after randomisation all participants will be invited to undertake outcome assessments. With participants’ consent, data on healthcare usage, long term conditions and medications will also be extracted from their medical notes. Approximately 20 intervention arm participants will also be asked to take part in a process evaluation interview after their 12-month assessment.

### Statistical methods

A detailed statistical analysis plan, including the health economic analysis, will be developed a priori and reviewed and approved by the Trial Steering Committee. All analyses will be by intention to treat. As missing data in the feasibility study were low and there are few gains to multiple imputation in RCTs [75, 76], imputation will not be used. We will descriptively summarise participants’ baseline characteristics using appropriate summary statistics (mean and SD, median and interquartile range or proportions) by randomised group.

The primary outcome (BI score at 12 months) will be analysed using linear mixed models, including 6 and 12-month data, controlling for baseline BI score and site (the stratification variable). Assumptions will be checked and appropriate transformations or analogous models will be used if the assumptions of linear models are violated. The ICC will be reported. Continuous secondary outcomes will be analysed using similar linear mixed models to the primary outcome, including 6 and 12-month data and controlling for outcome baseline score and site. Dichotomous outcomes (death and exhaustion) will be analysed using logistic regression. Falls will be analysed using Poisson regression or an analogous alternative if the assumptions for Poisson are not met. If it is not possible to use Poisson regression or an analogous alternative, then we will consider dichotomising falls and analysing in a similar way to other dichotomous outcomes. If there are too few events to perform statistical modelling for falls or the other dichotomous outcomes, they will be reported descriptively.

We will examine baseline predictors of missingness for the primary outcome and include any significant predictors of missingness in a supportive analysis to restore the missing at random assumption using a similar model to the primary analysis. All analyses will be complete case. We will also perform a complier average causal effects (CACE) analysis after unblinding using a threshold dosage of 3 + sessions for compliance to determine the average treatment effect of participants who would have adhered to the protocol regardless of how they were randomised.

For the process evaluation, we will carry out a number of exploratory analyses, including whether those who get a therapeutic dose of HomeHealth (3 + sessions) have higher BI at 12 months; whether choice of goal impacts on related outcomes (e.g. social goal and UCLA-3 score) and whether progress towards goals is associated with higher BI scores. If sufficient data are available, we will explore the impact of remote delivery vs. face to face delivery on outcomes. We will descriptively summarise service delivery data (e.g. appointments attended) and compare the demographics of those recruited to the expected population to assess intervention reach. Qualitative data will be analysed using codebook thematic analysis [77], involving multiple multidisciplinary team members (including Patient and Public Involvement and Engagement (PPIE)), and barriers and facilitators to implementation will be explored using Normalisation Process Theory [78].

For the health economic analysis, we will calculate the mean incremental cost per quality adjusted life years gained (QALYs) using EQ-5D-5L and the relevant UK tariff. QALYs will be calculated from the EQ-5D-5L as the area under the curve adjusting for baseline [74] with site as a fixed effect in line with the analysis of the primary outcome. We will also report Years of Full Capability (YFC) using ICECAP-O and its respective tariff for the duration of the trial. YFC will be calculated according to the most current guidance [79]. The primary analysis will be the incremental cost per QALY gained from a health and personal social services cost perspective, with secondary analyses reporting the incremental cost per YFC gained, and calculating incremental costs from a wider cost perspective to capture the impact on carers and any patient/carer out of pocket costs for health and social care. Means and 95% confidence intervals will be based on bootstrapped results. We will adjust difference in total cost at 12 months by baseline values [80] with site as a fixed effect and a random effect for therapist clustering.

EQ-5D-5L, ICECAP-O, QALYs and YFC, resource use and costs will be summarised descriptively. Cost-effectiveness acceptability curves and cost-effectiveness planes will be reported to represent the probability that the intervention is cost-effective compared to TAU for a range of cost-effectiveness thresholds for a QALY and YFC gained. Seemingly unrelated regression will be used to account for the correlation between costs and QALYs/YFC. A range of sensitivity analyses will be conducted for any assumptions. Procedures for handling missing data will follow those of the statistical analysis.

We will carry out a budget impact analysis, developing a tool for funders or commissioners to use to assess the yearly costs to their budget of implementing HomeHealth in a range of different commissioning models. Due to the paucity of long-term data upon which to base assumptions regarding effectiveness over time, we will explore alternative scenarios, including: 1) assuming constant effectiveness of the intervention over five years, 2) initial further gains in year 1–2 (if care home moves and hospital admissions are avoided) followed by a depreciation in effect, and 3) a slow decline in effectiveness over time. We will also include the impact of further assumptions such as the grade of intervention delivery staff, training costs and patient case load, taking into account the size and composition of the relevant local population. We will model scenarios for potential costs to the NHS if aspects of the intervention were commissioned by a third sector organisation, or if commissioned as part of publicly funded social care, the impact on local authorities.

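### The supportive missing-data model admits covariates only if they significantly predict missingness, which ignores prognosis and cannot restore missing at random

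*Protocol article*

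**What the plan says.** Under Statistical methods, the primary analysis is "linear mixed models, including 6 and 12-month data, controlling for baseline BI score and site (the stratification variable"). On missing data, the article argues that "there are few gains to multiple imputation in RCTs [75, 76], imputation will not be used". It then adds a supportive step. Baseline variables are first checked for an association with a missing 12-month BI, after which the analysts will "include any significant predictors of missingness in a supportive analysis to restore the missing at random assumption using a similar model to the primary analysis". The same paragraph states "All analyses will be complete case".

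No significance level or candidate list is given, and the article does not say whether the screen is run with arms combined or separately. Detail is deferred: "A detailed statistical analysis plan, including the health economic analysis, will be developed a priori". That plan is not shown.

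For scale, the Sample size section plans for losses, "so we have conservatively assumed 20% attrition over 12 months", with 386 randomised, SD 5 and a target difference of 1.85 BI points.

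**The concern.** The entry rule asks whether a baseline variable is associated with having a missing outcome. Whether leaving it out biases the arm comparison is a different question. For that, the variable must predict BI and its relation to dropout must differ between arms. The rule tests neither condition directly.

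A variable that raises dropout equally in both arms is readily detected, but adjusting for it removes no bias. A prognostic variable that acts on dropout in one arm only is diluted in a screen with arms combined. One that acts in opposite directions is nearly invisible there.

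Missing at random is also untestable from the observed data, so adding whatever passed a screen cannot restore it. The practical risk is that the supportive estimate lands close to the primary one because the needed variable was screened out, and the agreement is then read as reassurance.

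**Working it through.** **The plan's own figure.** n per arm = 2 × (1.96 + 1.2816)² × 5² / 1.85² = 153.5, so 154 per arm and 308 in total. 308 / 0.80 = 385, or 386 for equal arms. The stated size reproduces. Expected missing outcomes: 0.20 × 386 ≈ 77.

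**Power of the screen.** Take a baseline factor that splits the 386 participants in half (193 v 193), with 20% attrition overall and a two-sided 5% test. The level and the contrasts are assumptions. For 16% v 24% missing:
- SE under the null = √(0.20 × 0.80 × 2/193) = 0.0407
- SE under the alternative = √((0.16 × 0.84 + 0.24 × 0.76)/193) = 0.0405
- Power = Φ((0.08 − 1.96 × 0.0407)/0.0405) ≈ 50%

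The same calculation gives 31% for 17% v 23%, 69% for 15% v 25%, and 93% for 13% v 27%. Moderate predictors are often missed and strong ones are not.

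**When omission causes bias.** For a binary prognostic factor X with 50% prevalence, P(X=1 | observed) = (1 − p₁)/[(1 − p₁) + (1 − p₀)], where p₁ and p₀ are the proportions missing with and without X. Bias = (effect of X on BI) × (difference between arms in that probability). Take an assumed X effect of 2.5 points, which is a correlation of 2.5 × 0.5/5 = 0.25 with BI:

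| Pattern (p₀/p₁ in each arm) | P(X=1) observed | Bias, absolute |
|---|---|---|
| Rates differ by arm only, 15/15 v 25/25 | 0.500 v 0.500 | 0 |
| X acts equally, 15/25 v 15/25 | equal | 0 |
| X acts in one arm, 10/30 v 20/20 | 0.4375 v 0.500 | 0.16 |
| Opposite, 10/30 v 30/10 | 0.4375 v 0.5625 | 0.31 |

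In 2,000 simulated trials per pattern, a screen with arms combined selected X in 70% of one-arm trials, and bias fell from 0.15 to 0.04. It selected X in 4% of opposite-pattern trials, and bias stayed at 0.28. With X always included, bias was about 0 (Monte Carlo SE 0.01).

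**Continuous covariate.** Assume a correlation of 0.3-0.5 with BI, SD 5, 20% missing, and a 0.5-SD difference between missing and observed participants. Observed participants in an affected arm are then shifted by 0.20 × 0.5 = 0.10 SD.
- One arm: bias without the variable ≈ 0.3 × 5 × 0.10 = 0.15 to 0.5 × 5 × 0.10 = 0.25.
- Opposite directions: twice that, 0.30 to 0.50.

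Simulation of the screening rule, with 193 per arm and ordinary least squares at 12 months, gives:

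| Pattern | Screen misses | Bias left after screening | Type I error after screening |
|---|---|---|---|
| Equal in both arms | about 2% | about 0 | about 5% |
| One arm only | about 50% | about 0.08-0.15 | about 5.8% |
| Opposite | about 95% | about 0.26-0.46 | about 8-13% |

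Including the variable regardless of p gives bias of at most 0.02 and type I error of 4.7-5.4%.

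**Effect of the 6-month data.** The planned model uses both visits. Assume a baseline correlation of 0.6, a 6-12 month residual correlation of 0.7, and 6-month BI available for 50-70% of those missing at 12 months. Bias with the covariate always omitted is then 0.06-0.13 (one arm) and 0.12-0.27 (opposite). A separate two-visit simulation let half or all of those missing at 12 months also be missing at 6. After screening it gave 0.05-0.12 and 0.20-0.48. Someone who missed both visits contributes no 6-month BI, so the protection depends on how many do contribute it.

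**The case against.** The strongest reply is that this is one supportive analysis, described in a condensed article with a detailed analysis plan to follow, and that the primary model already carries much of the protection. Most of that stands. Baseline BI, site and 6-month BI are in the model, and the 20% is a planning allowance against 6% attrition in the feasibility study. At the feasibility SD of 3, with the same correlations, the biases scale by 3/5, to about 0.05-0.09 and 0.16-0.28.

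Several stronger readings are tempting, and the document does not support them:
- That the authors treat non-significance as proof that a variable is unnecessary. The article never says so; omission is only the effect of the rule.
- That unequal attrition between arms in itself biases the comparison. It does not, because arm is in the model; the calculated bias is 0.
- That the screen will usually miss the variable needed. This holds only for opposite relations and arms combined. In the one-arm pattern the variable is found in about 50-70% of trials, and nothing in the article makes the opposite pattern likely.
- That dropout is never examined by arm, or that no other missing-data analysis is planned. Either may be in the plan not shown.
- That the Limitations section foresees differential dropout. Its statement that "participants cannot be blinded to arm allocation, which may bias participant reported outcomes" concerns reporting, not attrition.

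What survives is the rule the article does state, selection on significance for missingness alone, and its claim to restore missing at random. Further detail in the analysis plan would not make that claim correct.

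**Conclusion.** The point holds as a minor one. The rule selects on the wrong criterion with limited power, and the stated purpose overclaims. Relative to the 1.85-point target, the bias left after screening is about 4-8% in the one-arm pattern (0.08/1.85 to 0.15/1.85). It is about 14-25% in the opposite pattern (0.26/1.85 to 0.46/1.85), which is an extreme case and not an expectation. With 6-month BI in the model these figures are generally smaller.

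The sizes rest on assumed covariate strength, an assumed 0.5-SD dropout shift, SD 5, 20% attrition, a 5% screen with arms combined, and dropout that depends on the covariate alone. If dropout is not at random given the measured variables, no choice of baseline covariates repairs it. The sizes also concern what the supportive analysis could fail to correct. They do not show that the primary estimate is biased.

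**What to change.** State in the analysis plan, before unblinding, that the supportive model includes a fixed set of baseline variables expected to predict 12-month BI, regardless of their p-value for missingness. Examples are age, Nottingham Extended ADL, Fried score and MoCA, with one common scoring for the face-to-face and telephone MoCA. Any predictors of missingness found are added to this set and do not replace it. Number of long-term conditions should not be listed as a baseline measure already in hand: Table 1 shows it as extracted from medical notes with no baseline tick, and extraction needs consent.

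Replace the claim to restore missing at random with a statement that the adjustment makes that assumption more plausible.

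The cost is a few degrees of freedom among about 308 participants and the loss of anyone lacking one of the chosen baseline values. No new data are needed, and the primary analysis and the 386 are unchanged.
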